#### Secondary outcome measures

##### Change in medians of MMAS-8 after three months

The difference in median MMAS-8 scores reported after three months between the intervention and the control group will be calculated. The effect size and the corresponding 95% CI will be reported. We will use a specific independent sample t-test on robust location measure (median) implemented in the function “medpb2” in Randy Wilcox’s R package WRS2 [93].

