## Methods

### Trial objectives

The primary objective of the SPPA trial is to assess if daily SMS reminders of antihypertensive medication intake provided by pharmacists in addition to the sPhC increase the proportion of adherent older hypertensive ambulatory patients.

Secondary objectives include: (1) comparing the change of self-reported adherence using the eight-item Morisky Medication Adherence Scale (MMAS-8); (2) comparing ARs measured via pill count between trial groups; (3) comparing the change in systolic blood pressure; (4) investigating the effect of SMS reminders on improving patients’ adherence and systolic blood pressure control (treatment effects) across subgroups; and (5) collecting and reporting patients’ satisfaction with daily SMS reminders.

We will report up-to-date ARs of older hypertensive patients in Slovakia and assess the impact of sociodemographic characteristics on patients’ adherence to antihypertensive medicines. Furthermore, we will evaluate the MMAS-8 questionnaire in our trial population. Additionally, we will carry out a simple cost-effectiveness analysis from the payers’ perspective.

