#### Secondary outcome measures

Table 4 summarizes the details of our secondary outcome measures. We will also evaluate the clinical outcome – blood pressure, which is highly emphasized to provide information on the relationship between medication adherence and blood pressure control [33]. Considering our trial population, consisting of older patients, we have decided to evaluate only systolic blood pressure, not diastolic blood pressure, in our secondary clinical outcome. First, diastolic blood pressure is known to paradoxically decrease with increasing age in patients aged above 55 years [78]. Second, diastolic blood pressure has shown to be less predictive in regard to decrease in cardiovascular morbidity and mortality [79]. We prepared a detailed guidance for blood pressure measurement (SPPA Scheme for Blood Pressure Measurement is available within Additional file 3) based on the current international recommendations for blood pressure measurement [4, 80]. Trial pharmacists will be re-trained on all steps and will comply with the SPPA Scheme for Blood Pressure Measurement during the whole trial, which will ensure that all blood pressure measurements will be performed uniformly.

**Table 4 Tab4:** Secondary outcomes

Secondary outcome	Change in medians of MMAS-8	Mean adherence rate after 3 months	Mean change in systolic blood pressure
Domain	Self-reported medication adherence (MMAS-8 questionnaire)	Medication adherence (pill count)	Blood pressure (manometer)
Specific measurement variable	MMAS-8 (categorical, ordinal)	Adherence rate in % (numerical, continuous)	Systolic blood pressure in mmHg (numerical, continuous)
Analysis Metric	Change from baseline (Visit 1)	Final value (Visit 2)	Change from baseline (Visit 1)
Method of aggregation	Median	Mean	Mean
Time point of measurement	Visit 1 Visit 2	Visit 2	Visit 1 Visit 2

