The planned sample size is sufficient to detect a difference in adherence of 1 point on the MMAS-8 scale, which is our secondary outcome. Provided that the median MMAS-8 score in the control group is 4 and in the intervention group 5 (SD = 1.8) [30], using a two-tailed t-test, we need 172 participants to achieve a power of 95% and significance level of 5%. For our secondary clinical outcome (mean change in systolic blood pressure), this sample size lacks sufficient power to detect a clinically meaningful change of at least 5 mmHg (SD = 20) with a power = 0.9, alpha = 0.05 (using either mixed analysis of variance or analysis of covariance test). A larger sample is currently not feasible; however, the SPPA trial focuses primarily on adherence to medication. If the results of this trial show sufficient effectiveness of SMS reminders in increasing prevalence of adherent older hypertensive patients and patients’ satisfaction is high, we will conduct a larger study focusing on clinical outcomes. Sample size calculations were carried out using G*Power software version 3.1.9.2.

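### The MMAS-8 secondary outcome is defined as change from baseline but tested on Visit 2 medians alone, and its figure of 172 patients for 95% power belongs to a t-test, not to the planned median test

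*Protocol article*

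**What the plan says.** Four places in the protocol article bear on this outcome.

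- **Trial objectives.** The first secondary objective is "comparing the change of self-reported adherence" on the MMAS-8.
- **Secondary outcome measures, Table 4.** The analysis metric for MMAS-8 is "Change from baseline (Visit 1", measured at both visits and aggregated as a median.
- **Change in medians of MMAS-8 after three months.** Despite the heading, the estimate is the Visit 2 contrast: "The difference in median MMAS-8 scores reported after three months between the intervention and the control group will be calculated". The test is a "specific independent sample t-test on robust location measure (median) implemented in the function" medpb2 of the R package WRS2.
- **Sample size calculation.** The article states: "The planned sample size is sufficient to detect a difference in adherence of 1 point on the MMAS-8 scale". The inputs are medians of 4 and 5 with an SD of 1.8, and "using a two-tailed t-test, we need 172 participants to achieve a power of 95% and significance level of 5" per cent.

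**The concern.** The metric and the analysis do not describe the same quantity. Three readings are open: a difference between arms in Visit 2 medians, a difference in the change of each arm's median, or a difference in the median of individual changes. A median of changes is in general not a change in medians, so the last two can differ. If the choice stays open until the data are seen, it can be made with knowledge of the result.

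The article handles its other two measured secondary outcomes consistently. Systolic pressure, which has the same change-from-baseline metric in Table 4, is analysed by methods that use both visits. Pill count, a final-value outcome, is compared at Visit 2 only. MMAS-8 is labelled like the first and analysed like the second.

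The power statement also concerns a test that will not be run. A t-test compares means, whereas medpb2 compares medians by percentile bootstrap. For roughly normal data a median is a less efficient summary than a mean, so the sample size for one does not carry over to the other.

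**Working it through.** **Inputs from the article.** Difference 1 point, SD 1.8, two-sided alpha 0.05, target power 0.95 (Sample size calculation). 264 patients needed for the primary outcome; 300 enrolled with about 10% attrition, so 300 × 0.9 = 270 evaluable (same section). MMAS-8 has seven yes/no items and one five-point item, range 0 to 8 (Primary outcome measure).

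**Assumptions, not in the article.** The shape of the score distribution, and the correlation r between baseline and Visit 2 scores, taken as 0.3 to 0.7.

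**Step 1: reproduce the stated figure.** d = 1/1.8 = 0.556. Normal approximation per arm: 2 × (1.960 + 1.645)² / 0.556² = 84.2, so 85 per arm (170 in total). The exact calculation with the noncentral t gives 172 in total, power 0.952. The article's figure is correct for a t-test.

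**Step 2: the same inputs with the planned test.** For normal scores the standard error of a median is √(π/2) = 1.253 times that of a mean. The standard error of the difference in medians is 1.8 × 1.253 × √(4/N) = 2.256 × √(4/N).

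- N = 172: 2.256 × 0.1525 = 0.344; 1/0.344 − 1.960 = 0.947; power 0.828.
- N for 95% power: 84.2 × π/2 = 132.3, so 133 per arm, 266 in total.

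**Step 3: power at the planned size.** The simulated columns use a percentile-bootstrap test of two medians, 1,200 runs each. The mixed-item score is built like MMAS-8, with seven binary items and one item scored in quarter points.

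| Total N | t-test (exact) | Median test, formula | Simulated, normal | Simulated, mixed-item | Simulated, whole points only |
|---|---|---|---|---|---|
| 172 | 0.952 | 0.828 | 0.82 | 0.82 | 0.48 |
| 264 | 0.994 | 0.950 | 0.956 | 0.948 | 0.70 |
| 270 | 0.995 | 0.954 | – | – | – |
| 300 | 0.998 | 0.970 | 0.966 | 0.968 | 0.75 |

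Simulation error is about one percentage point. Across the simulation variants, including normal scores rounded to quarter points and limited to 0–8, the median test lies at about 0.79 to 0.84 at N = 172. The rounded variant was the lowest and gave about 0.93 at N = 264.

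**Step 4: what baseline adjustment would add.** ANCOVA reduces the residual SD to 1.8 × √(1 − r²).

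| r | ANCOVA power, N = 172 | ANCOVA power, N = 264 |
|---|---|---|
| 0.3 | 0.967 | 0.997 |
| 0.5 | 0.987 | 0.999 |
| 0.7 | 0.999 | above 0.999 |

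**Step 5: the choice of metric matters.** If the median test were applied to individual change scores, as Table 4 can be read, the SD would be 1.8 × √(2(1 − r)). Treating change scores as normal, power at N = 264 would be 0.861, 0.950 and 0.996 for r = 0.3, 0.5 and 0.7. The sizing text gives no SD of change, so its calculation fits the Visit 2 comparison and not the metric in Table 4.

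**The case against.** The strongest reply is that the conclusion in the sample size section concerns the planned size, and 172 is only the minimum for this outcome. That stands. At 264 to 300 patients the median test has roughly the power claimed under the article's own inputs.

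It can also be said that under 1:1 randomisation the baseline medians are equal in expectation, so a Visit 2 contrast targets the same population value as a difference in change of medians. That stands too, for that reading of the outcome. The sizing, stated as a score per arm, agrees with the analysis section on this.

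Four stronger readings are tempting, and the documents do not support them.

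- **That the outcome is underpowered.** This requires scores to fall almost entirely on whole points. The five-point item allows fractional scores, and no distribution is given.
- **That the Visit 2 comparison is biased.** Randomisation protects it; the loss is in precision and clarity.
- **That baseline MMAS-8 goes unused.** The Subgroup analysis section uses it as a subgroup factor. It is absent only from this outcome's test.
- **That a bootstrap median test cannot be combined over imputed data sets.** The bootstrap yields a median difference and a spread that can serve as its standard error, and the section promises a confidence interval. The pooling details can be left to an analysis plan.

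Finally, Table 4 calls the scale ordinal and chooses the median, so moving to a model changes the effect measure. That is a real cost, stated under the fix.

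**Conclusion.** The point holds as a mismatch that should be corrected. It does not invalidate the outcome. Objective 1 and Table 4 specify change from baseline, while the analysis compares Visit 2 medians without a baseline term. The result would be unbiased but less precise than the collected data allow.

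The pairing of 172 participants with 95% power is wrong for the planned test: about 79% to 84% at 172, and about 266 patients for 95%. At 264 to 300 patients the power is about 94% to 97%, so the statement of sufficiency survives. This rests on SD 1.8 and roughly normal or quarter-point scores. If scores cluster on whole points, power is about 70% at 264 and 75% at 300; this is a possibility to guard against and not a finding about this trial. The gain from adjustment depends on the assumed correlation of 0.3 to 0.7.

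**What to change.** 1. Name one metric for MMAS-8 in the objectives, Table 4, the sample size section and the analysis section.
2. Make the main analysis a comparison of Visit 2 MMAS-8 between arms adjusted for baseline MMAS-8. ANCOVA with robust standard errors, or a proportional-odds model given that Table 4 calls the scale ordinal, would serve. The article already plans a baseline-adjusted analysis for systolic pressure.
3. Keep the difference in medians from medpb2 as a supporting summary.
4. Restate the power for the test actually used at about 264 to 270 evaluable patients, with the assumed score distribution and, for an adjusted model, the assumed baseline correlation.

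The cost is wording in these places; no new data or patients are needed. The downside is that the main effect measure becomes an adjusted mean difference or an odds ratio and is no longer a difference in medians. If the sponsor prefers to keep the median test as the main analysis, the least that is needed is to change Table 4 and objective 1 to a final-value metric and to replace the t-test power figure.

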#### Mean adherence rates after three months calculated via pill count

The mean difference in adherence reported as AR (%) measured at Visit 2 between the intervention and the control groups will be calculated. The effect size and the corresponding 95% CI will be reported. We will use a two-tailed t-test to compare the difference between these independent means as well as their robust versions that are recommended when conditions for these tests are violated while preserving high statistical power.

#### Mean change in systolic blood pressure

For the clinical secondary outcome, the results of a mixed analysis of variance (suitable to assess change in pre and post measurements) and analysis of covariance (suitable to assess the differences in pre and post measurements) as well as their robust versions, that are recommended when conditions for these tests are violated while preserving high statistical power, will be compared [94].

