### Statistical analysis

We will conduct all analyses according to the intention-to-treat principle, striving to collect data from all participants. In case of missing data, data imputation techniques (multivariate imputation via chained equations) will be used. Predictive mean matching and logistic regression [86] will be used for continuous (e.g. systolic blood pressure) and categorical (e.g. MMAS-8) variables, respectively. For comparison, a per-protocol analysis will also be carried out. We will comprehensively report all missing data along with the reasons why these data are missing and explore their patterns. This information will help us to appropriately adjust future study protocols. No interim analysis is planned. Descriptive statistics will be reported as means (SD) or medians (interquartile range) for continuous variables and proportions for categorical variables. All statistical analyses will be carried out with a 5% type I error rate.

Results of the SPPA trial will be reported following the Consolidated Standards of Reporting Trials (CONSORT) 2010 statement [87, 88] and the Guidelines for reporting of health interventions using mobile phones: mobile health (mHealth) evidence reporting and assessment (mERA) checklist [36]. All analyses will be conducted with R software [89] using the basic statistical functions as well as robust functions from the package WRS2 [90] and for plotting and graphs the ggplot2 package [91].

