The three-month intervention period is relatively short to ensure long-lasting clinical improvement and the potential benefits may wear off with time. However, once the initial clinical benefit, feasibility, patient acceptance, and cost-effectiveness are proven in this trial, we plan to conduct follow-up research to address these limitations.

A limitation to the pragmatic trial design is also that the external unblinded trial pharmacist is sending the SMS reminders centrally. We have accepted this limitation to ensure the blinding of the trial pharmacists as assessors of patients’ adherence, which is the primary objective of the current trial.

The SPPA trial will be the first registered pharmaceutical clinical trial in Slovakia. Understanding the need of evidence-based pharmaceutical care (EBPC) [57, 104], we aim at improving the quality of pharmaceutical care through EBPC also in the currently presented trial. SPPA trial addresses the main healthcare challenges not only in the Slovak Republic: high prevalence of hypertension and other secondary cardiovascular diseases, overconsumption of cardiovascular drugs, alarmingly low AR to long-term medication treatment, and high rates of uncontrolled blood pressure. In countries, whose healthcare systems lack financial resources and healthcare professionals, similar to the Slovak Republic, a simple mHealth intervention in form of SMS reminders of medication intake provided by pharmacists may be an efficient way to address all of these problems.

The SPPA trial will provide essential information to design future studies assessing mHealth technologies through EBPC. Therein, we will concentrate on clinically important outcomes, provided that the SPPA trial shows promising results in improving systolic blood pressure. The focus on objective clinical outcome will also enable directly the pharmacists to send the SMS reminders to patients without the need to remain blinded. Moreover, we will adjust the intervention to better reflect patients’ needs using the collected patient reported outcomes in the presented trial. Detailed publicly available reporting of the SPPA trial will serve as a source of valuable information on methodology, design, and conduct of pragmatic clinical trials in community pharmacies.

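### Systolic blood pressure is to be analysed by mixed ANOVA, ANCOVA and robust versions of both, and none is named as the result

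*Protocol article*

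**What the plan says.** The subsection of the protocol article on mean change in systolic blood pressure names two classical models, "the results of a mixed analysis of variance (suitable to assess change in pre and post measurements) and analysis of covariance", and adds the robust counterparts: "as well as their robust versions, that are recommended when conditions for these tests are violated while preserving high statistical power, will be compared". It names no lead analysis and gives no rule for the case where they disagree.

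The sample size section leaves the same choice open, "using either mixed analysis of variance or analysis of covariance test", when it states that the trial lacks power for a "clinically meaningful change of at least 5 mmHg (SD = 20) with a power = 0.9, alpha = 0.05". Table 4 fixes only the metric, mean change from baseline, and that does not select a model. The general statistical section states: "All statistical analyses will be carried out with a 5% type I error rate". Randomisation is stratified by sex within each centre.

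Two places say what would lead to the next study. The sample size section relies on adherence and satisfaction: "If the results of this trial show sufficient effectiveness of SMS reminders in increasing prevalence of adherent older hypertensive patients". The Discussion says later studies will concentrate on clinical outcomes "provided that the SPPA trial shows promising results in improving systolic blood pressure".

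**The concern.** The article describes the two classical models as if they suited different questions, one for change and one for differences. In a randomised trial with a single pre and a single post measurement, both estimate the same between-arm effect. The plan therefore allows up to four p-values for one question.

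Two things are at stake. First, a reader of the results could not tell which p-value and interval the 5% level refers to, and nothing in the text stops the most favourable one from being put forward. Second, one of the two classical models is less precise than the other for an outcome where the article already admits it is short of power.

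**Working it through.** **Inputs.** From the article: difference 5 mmHg, SD 20, alpha 0.05, 1:1 allocation, 264 evaluable patients required, 300 enrolled with about 10% attrition. The attrition gives 300 × 0.9 / 2 = 135 per arm. Assumed: two-sided tests, equal variance at both visits, and a correlation r between visits, which the article does not give (range shown).

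**The article's own figures.** The chi-square calculation with w = 0.2 and 90% power gives N = 263, or 264 for equal arms, as stated. The MMAS-8 t-test (1 point, SD 1.8, 95% power) gives 172, as stated. No sample size is stated for systolic pressure. An unadjusted comparison of 5 mmHg with SD 20 at 90% power needs about 674 to 676 patients, so the admission of low power is fair on that basis.

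**Precision.** In units of the single-visit variance, the change score has variance 2(1−r) and the ANCOVA residual has variance 1−r². The ratio is (1−r²) / [2(1−r)] = (1+r)/2: 0.75, 0.80 and 0.85 at r = 0.5, 0.6 and 0.7. It is below 1 for every r below 1.

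**Power at 135 per arm (noncentral t).** The article does not say whether SD 20 refers to a single visit or to the change, so both readings are shown.

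| r | SD 20 single visit: ANCOVA | SD 20 single visit: change score | SD 20 of change: ANCOVA | SD 20 of change: change score |
|---|---|---|---|---|
| 0.5 | 65.7% | 53.5% | 65.7% | 53.5% |
| 0.6 | 72.5% | 62.9% | 62.9% | 53.5% |
| 0.7 | 81.7% | 75.2% | 60.3% | 53.5% |

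Under the first reading the SDs used are 20√(1−r²) and 20√(2(1−r)). Under the second they are 20√((1+r)/2) and 20.

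**False positives, two classical models.** With no effect, the change-score estimate is D_Y − D_X and the ANCOVA estimate is D_Y − r·D_X, where D_Y and D_X are the arm differences at follow-up and baseline. Their covariance is proportional to 1−r², so their correlation is (1−r²)/√[2(1−r)(1−r²)] = √((1+r)/2). The bivariate normal probability that at least one exceeds 1.96 in absolute value is:

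| r | Correlation of the tests | At least one significant |
|---|---|---|
| 0.3 | 0.806 | 7.8% |
| 0.4 | 0.837 | 7.6% |
| 0.5 | 0.866 | 7.3% |
| 0.6 | 0.894 | 7.1% |
| 0.7 | 0.922 | 6.8% |

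**False positives, all four.** This was simulated: 132 per arm, 2,500 null trials per setting, Monte Carlo error about 0.4 to 0.6 points. The stand-ins were a 20% trimmed-mean test on change and, for robust ANCOVA, either Huber regression or trimmed means at five baseline points with Bonferroni. With normal data and r = 0.3, 0.5, 0.7 and 0.8, at least one of four was significant in 10.8%, 9.8%, 9.7% and 7.7% (Huber), or 12.2%, 10.9%, 11.6% and 9.8% (trimmed). Heavy-tailed data at r = 0.3 and 0.5 gave 10.6% to 11.7%. Each test on its own stayed between 4.3% and 6.2%, so designating one restores about 5%.

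**The case against.** The strongest reply is that the article promises to compare results, which implies showing all of them. Showing several analyses does not change the error rate of any one. A reader might infer that the plan as written inflates false positives. The text does not support that: inflation needs a favourable result to be picked out, and the article plans no such selection. What remains is that it does not rule selection out either.

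The robust versions also have a stated role, as methods recommended when assumptions fail, which points towards a check and not a test of equal standing. That is reasonable, but no criterion for failure is given, and the choice between mixed ANOVA and ANCOVA stays open either way.

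The choice of a lead model could be left to a statistical analysis plan that is not shown. Silence would be excusable on that ground. Here, however, the article itself commits to competing models.

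Two further inferences go too far. One is that the next trial hinges on a blood-pressure test, in contradiction to the sample size section. The Discussion speaks only of promising results, with no threshold, and the two conditions could both apply. The other is that the pill-count analysis has the same flaw. There the article puts the two-tailed t-test first and the robust version after it, so a lead analysis can be read from the text.

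**Conclusion.** The point stands as a gap in how the analysis is fixed: one between-arm question, two classical models and their robust versions, and no designated result. ANCOVA is the better of the two classical models under randomisation, whatever the correlation. How much power it gains depends on r and on what SD 20 means: about 6 to 12 percentage points under the single-visit reading, and about 7 to 12 under the SD-of-change reading, for r from 0.5 to 0.7.

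The possible inflation is moderate because the tests are highly correlated, and it is conditional on any result being citable. The two-model figure follows from r alone; the four-model figure is only indicative because it rests on stand-ins. The outcome is secondary and declared underpowered, and the primary between-arm comparison of adherence is untouched. The differing statements about the next study are an editorial matter and change nothing that this trial would conclude.

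**What to change.** Name one analysis: ANCOVA of Visit 2 systolic pressure on arm and baseline systolic pressure, with the randomisation strata sex and centre, reported as the adjusted difference with its 95% CI. Table 4 can keep its metric, because with baseline in the model the arm difference is the same whether the outcome is the Visit 2 value or the change. Label the mixed ANOVA, if it is kept, and the robust versions as sensitivity analyses that do not replace the result if they disagree. Name the same model in the sample size section, and say there whether SD 20 is that of a single visit or of the change.

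As a minor editorial step, bring the sample size section and the Discussion into line on what would lead to the next study.

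The cost is wording only: no new data, patients or procedures.
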